### Intravascular Ultrasound and Virtual Histology

All IVUS imaging will be performed using a 20-MHz 2.9F, phased-array IVUS catheter (Eagle Eye, Volcano Therapeutics, Rancho Cordova, CA) after first administering nitroglycerin (200 mg). The IVUS catheter is placed distal to the target lesion, and then pulled back using a motorized pullback system at 0.5 cm/s. During pullback, grayscale IVUS is recorded and raw radiofrequency data are captured at the top of the R wave for reconstruction of the color-coded map by a VH-IVUS data recorder (Volcano Therapeutics). For evaluation of the index intermediate lesion, a segment at least 30 mm in length will be evaluated with IVUS and VH at baseline and 9-month follow-up. The most severe 10-mm segment centered on the minimal lumen area will be analyzed for plaque volume and plaque composition (fibrotic, fibrofatty, dense calcium, and necrotic core components). The index PCI target lesion will be evaluated for neointimal growth with grayscale IVUS after PCI and at 9-month follow-up. IVUS evaluation will include 5-mm segments proximal and distal to the stent. IVUS and VH images will be analyzed by an independent core laboratory (Cardiac Core Analysis Laboratory at Stanford University Medical Center, Stanford, CA).

### Laboratory assessment

Blood samples will be obtained after overnight fasting. Serum lipids, apolipoproteins, hs-CRP, Lp(a), oxidized LDL, VCAM-1, and vWF levels will be measured at a central clinical laboratory (Seoul Clinical Laboratories, Seoul, Korea). Serum total cholesterol, LDL, HDL, and triglyceride levels will be measured using standard enzymatic methods. Apolipoprotein A-1 and B concentrations will be measured by turbidimetric immunoassay methods. Serum oxidized LDL, VCAM-1, and vWF levels will be measured using enzyme-linked immunosorbent assays. Serum hsCRP and Lp(a) levels will be measured using latex-enhanced turbidimetric immunoassays. The particle-size distribution of LDL isolated by sequential flotation ultracentrifugation will be determined using a pore-gradient lipoprotein system (CBS Scientific, CA) at the National Research Laboratory for Clinical Nutrigenetics/Nutrigenomics, Yonsei University, Seoul, Korea, as previously described [26]. Circulating HDL subfractions HDL2 and HDL3 will be quantified after ultracentrifugation of serum at the Laboratory of Nutritional Medicine/Nutrigenomics, Sungshin Women's University, Seoul, Korea, as previously reported [27].

### Study end points

The primary end point is the change in the plaque volume of index intermediate lesions between baseline and 9-month follow-up.

The secondary end points include the following:

• Plaque composition change by VH

• Clinical outcomes (death, myocardial infarction, target vessel revascularization)

• Neointimal volume obstruction at index PCI target lesions

• Blood lipid composition (total cholesterol, LDL, LDL particle size, HDL, HDL subfractions, apolipoprotein A-1 and B)

• Biomarkers (hsCRP, VCAM-1, oxidized LDL, Lp(a), vWF)

### Statistical considerations

#### Sample size calculation

The calculation of the sample size was based on an in-equality design and a two-sample, two-sided test. Assuming a standard deviation of 8%, an α-level of 0.05 and a statistical power of 80%, 41 patients are required for each group (combination therapy, cilostazol monotherapy) to demonstrate a 5% difference in the mean plaque volume in a 10-mm segment with the greatest disease severity of the index intermediate lesion. Making allowance for a drop-out rate of 30% increases the number of patients required for each group to 59. The treatment difference and standard deviation assumptions are based on previous clinical and animal studies. Several IVUS studies have successfully demonstrated the effect of statins in reducing plaque volume. Yokoyama et al. [22] showed a 3.2% reduction in plaque volume in patients treated with atorvastatin (10 mg/day) for 6 months. The ASTEROID trial achieved about a 25% reduction in the normalized total atheroma volume using rosuvastatin (40 mg/day) for 24 months [28]. Recently, Tardif at al. [29] reported that a 12-month therapy with succinobucol, an analog of probucol, reduced the plaque volume of index lesions by 1.5%, whereas the control group showed no significant change in plaque volume. Notably, the results of an animal study evaluating the antiatherogenic effects of cilostazol and probucol showed that combination therapy was more effective in reducing the size of atherosclerotic lesions than was administration of either drug alone [18]. For this reason, we expect that cilostazol and probucol combination therapy will be more potent in reducing plaque volume than succinobucol, and hypothesize that the combination therapy could achieve a reduction in plaque volume 5% greater than that achieved by cilostazol monotherapy.

### Statistical analysis

All statistical analyses will be carried out by an independent organization, ADM Korea Inc. All primary and secondary end points will be analyzed on a modified intention-to-treat basis (all randomized subjects who receive at least one dose of study drug and have IVUS and VH measurements at baseline and at the study end point). The primary efficacy analysis will be performed using an analysis of covariance model, adjusting for baseline values. If the data are not distributed normally, a nonparametric analysis of covariance analysis will be used. All continuous secondary efficacy variables will be analyzed using similar methods. The composite end point of cardiovascular events will be analyzed by comparing Kaplan-Meier event rates using a log-rank test. Independent predictors of major adverse cardiac events (MACE) were determined using a multiple logistic regression analysis.

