## Methods/design

### Study Design

This is a double-blind, placebo-controlled, randomised, multicenter clinical trial to evaluate the efficacy of probucol and cilostazol combination therapy compared with cilostazol alone in the prevention of coronary plaque progression (Figure 1). A total of 118 patients (see Sample size calculation, below) will be enrolled at five PCI centers in Korea. After enrollment and baseline investigation with IVUS and VH to establish index non-PCI target intermediate lesions and stented PCI target lesions, patients will be evaluated in clinical follow-up visits at 1, 3, 6, and 9 months. In the final 9-month follow-up examination, patients will be evaluated by IVUS and VH to assess plaque volume and plaque composition in index non-PCI target intermediate lesions, and measure neointimal hyperplasia in index stented PCI target lesions. Lipid profiles, to include total cholesterol, LDL, HDL, triglyceride, apolipoprotein A-1 and B, LDL particle size and HDL subfractions, and biomarkers associated with atherosclerosis, including high-sensitivity C-reactive protein (hsCRP), oxidized LDL, VCAM-1, von Willebrand factor (vWF) and lipoprotein (a) [Lp(a)], will be measured at enrollment, and at 1- and 9-month follow-up examinations. The trial algorithm is shown in Figure 1. This is an investigator-initiated clinical trial with grant support from Korea Otska Pharmaceutical Co. Ltd (Seoul, Korea). Other than providing financial support, the company is not involved in developing study protocols or study processes, including site selection, management, and data collection and analysis. The study is performed according to the principles of the Declaration of Helsinki and according to common guidelines for clinical trials (ICH-GCP). The authors are solely responsible for the design and editing of this paper and its final content. The trial protocol has been approved by the local institutional review boards of each patient-enrolling center, and has been registered at http://www.clinicaltrials.gov (NCT01031667). Patient information, blood samples, and IVUS, VH and coronary angiogram images will be coded with the identification number of this study; investigators are blinded to patient identifying information, which has been replaced with a coded number.

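### One analysis set that requires 9-month IVUS and VH is applied to every end point, so deaths cannot be counted in the clinical outcome and usable blood data are discarded

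*Protocol article*

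**What the plan says.** The Statistical analysis section fixes one population for the whole trial: "All primary and secondary end points will be analyzed on a modified intention-to-treat basis". It defines that population as randomised subjects who "receive at least one dose of study drug and have IVUS and VH measurements at baseline and at the study end point". The Study Design section sets the time of the second imaging: "In the final 9-month follow-up examination, patients will be evaluated by IVUS and VH".

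The Study end points section lists among the secondary end points "Clinical outcomes (death, myocardial infarction, target vessel revascularization", together with blood lipids and biomarkers. For the events, the Statistical analysis section plans a time-to-event comparison: "The composite end point of cardiovascular events will be analyzed by comparing Kaplan-Meier event rates using a log-rank test". The Study Design section says that the lipids and biomarkers "will be measured at enrollment, and at 1- and 9-month follow-up examinations". The article names no other population for clinical events or blood measures.

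**The concern.** A second IVUS and VH examination is needed to compute a change in plaque volume or composition. It is not needed to know whether a patient died, had an MI, was revascularised or gave a blood sample at 1 month. Making it a condition for all of these selects patients on something that happens after randomisation. For death, the condition and the outcome exclude each other.

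What is at stake is the clinical-outcome comparison, which would list death as a component but could not show one. The Background section reports QT prolongation with probucol and its withdrawal from many markets, so readers will look at deaths by arm. The lipid and biomarker comparisons would also lose information that the trial has already collected.

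**Working it through.** **Inputs from the article.** SD 8%, difference 5%, two-sided alpha 0.05, power 80%, 41 per group, 30% drop-out, 59 per group, 118 in total (Sample size calculation); clinical visits at 1, 3, 6 and 9 months and closing imaging at 9 months (Study Design). The article gives no event rates.

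**The plan's own figures.** n per group = 2 × (1.960 + 0.842)² × 8² / 5² = 40.2, rounded up to 41. With drop-out: 41 / 0.70 = 58.6, rounded up to 59, so 118 in total. These reproduce and are not at issue.

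**Patients leaving every analysis.** 118 − 2 × 41 = 36, and 36 / 118 = 30.5%. Under the stated rule these patients are absent from the imaging, clinical and blood end points alike.

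**Deaths.** Membership requires imaging at the final visit. A patient who dies earlier has none and is not a member. Planned follow-up ends at that visit, so in effect no death can be counted in either arm, whatever the true number.

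**Kaplan-Meier.** Every member has reached the 9-month imaging, so no member is censored earlier for loss or removed by death. The estimate at 9 months is then simply the number of members with a non-fatal event divided by the number of members.

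**MI and TVR.** These patients stay in the set if they have the 9-month imaging and leave it if they do not. Let d be the 9-month death rate, m the rate of non-fatal events, and p the share of non-fatal event patients without that imaging. With 30% missing imaging overall:

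- rate in all randomised patients = d + m
- rate shown by the set as written = m × (1 − p) / 0.70

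All values of d, m and p below are assumptions.

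| d + m | All randomised | p = 30% | p = 50% | p = 80% |
|---|---|---|---|---|
| 1% + 5% | 6.0% | 5.0% | 3.6% | 1.4% |
| 2% + 8% | 10.0% | 8.0% | 5.7% | 2.3% |
| 3% + 12% | 15.0% | 12.0% | 8.6% | 3.4% |

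For example, 0.08 × (1 − 0.5) / 0.70 = 5.7%. The composite is understated at every setting in the table, but that depends on p. The two rates are equal at p = 1 − 0.70 × (d + m) / m. For 2% + 8% this is 1 − 0.70 × 0.10 / 0.08 = 12.5%. If event patients missed imaging less often than that, the set would overstate the composite. The loss of deaths does not depend on p.

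**Blood measures.** Samples are due at enrollment, 1 month and 9 months. A patient with the first two but no second IVUS has a valid baseline-to-1-month change that the rule excludes. How many of the 36 would be in this position cannot be derived from the article.

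**The case against.** **A change in plaque volume needs two measurements.** This stands. A paired-imaging set is reasonable for the imaging end points, and the article defines its modified intention-to-treat set openly in the same sentence.

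**A condensed article leaves analysis sets to the full protocol or the SAP.** This does not stand here. The article does not leave the set open; it states one and applies it to all end points. An SAP that used another set for events would contradict it.

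**The defect is confined to secondary end points, and drop-outs would be censored in any case.** Both parts stand. The trial is sized on plaque volume, and with a wider set not all 118 patients would give full follow-up.

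Three stronger readings are tempting, and the article does not support them:

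- A reader might infer that all event patients are removed because of their outcome. That is certain only for deaths. Nothing in the article bars a patient with MI or TVR from the 9-month imaging.
- A reader might infer that the primary comparison is biased because the worst progressors are lost. The index intermediate lesion is by definition one that does not require PCI, and the article gives no rate of later revascularisation. Any shift computed for the treatment difference rests on unsourced assumptions about how loss differs between arms: similar loss in both arms could leave the difference unchanged, and the opposite pattern would reverse the sign.
- A reader might infer that deaths would go unreported. The rule governs this efficacy comparison. The article does not say how safety events are reported otherwise, and that silence is no evidence.

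**Conclusion.** Wrong as written, for the secondary end points. Three consequences follow from the text alone: no death before the 9-month imaging can be counted; the Kaplan-Meier estimate becomes a proportion of non-fatal events among imaged survivors; and valid 1-month blood data are excluded for patients without a second IVUS.

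The scale of the exclusion is about 36 of 118 patients (30.5%), if the planned 30% drop-out occurs and shows up as missing final imaging. The size and direction of any between-arm bias cannot be computed, because the article gives no event rates; the tabulated rates illustrate the mechanism under assumed values. The sizing and the covariance-adjusted primary analysis are not called into question.

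**What to change.** Replace the single population sentence in the Statistical analysis section, and carry the change into the full protocol and SAP, with three sets:

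1. **Clinical outcomes (death, MI, TVR):** all randomised patients, in the group to which they were randomised, with time counted from randomisation and censoring at last contact, and no imaging condition.
2. **Lipids and biomarkers:** all randomised patients with a baseline sample and at least one later sample.
3. **IVUS and VH end points:** the present paired-imaging set, kept for these end points only and described as a completer set.

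The cost is a little more programming and different denominators across end points, which the results tables should show. No new visits are needed, because the 1-, 3-, 6- and 9-month visits already provide the clinical follow-up. The sample size does not change.

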### Study population and Randomisation

Patients more than 20 years of age who have had at least one significant coronary artery stenosis requiring PCI with stent implantation and one intermediate lesion on a native coronary artery with luminal narrowing of ≥ 30% and ≤ 70% by visual estimation, and who also meet all inclusion and exclusion criteria (Table 1) are eligible for this study. Those who agree to participate in the study and give written consent are randomised (1:1) to either cilostazol and probucol combination therapy or cilostazol monotherapy (control) using a web-based online randomization system. The randomization is stratified by enrolling site and the presence of diabetes in order to ensure an even distribution between the two groups of major factors that might contribute to the primary end point. After enrollment, all patients will receive a starting dose of 20 mg simvastatin. The dose of simvastatin will be adjusted to reach a target LDL level of < 100 mg/dL. Concomitant use of other drugs that interfere with serum lipid levels, such as niacin, CETP or lipoprotein-associated phospholipase A2 (Lp-PLA2) inhibitor, fenofibrate or omega-3, is not allowed.

**Table 1 T1:** Patient Inclusion and Exclusion Criteria

Inclusion criteria
1. Male or female over 20 years of age
2. Clinical indication for coronary angiography
3. Presence of at least one significant coronary artery stenosis (>50%) requiring PCI with stent implantation and one intermediate lesion with luminal narrowing of ≥30% and <70% by visual estimation on native coronary arteries.
4. Presence of at least one PCI target lesion (reference diameter 2.5~4 mm, lesion length ≤26 mm) with >50% diameter stenosis that can be covered with a single Zotrolimus-eluting stent (Endeavor Sprint, Medtronic Vascular Inc, Santa Rosa, CA).
5. Able to understand and willing to provide written informed consent
Exclusion criteria
1. Intermediate lesions that might provide difficulty for IVUS evaluation because of following reasons: heavy calcification (>90° Arc), tortuous vessel with severe angulation, total occlusion, or bifurcation lesions
2. Previous PCI in the last 6 months
3. Previous coronary artery bypass graft
4. Patients with AMI undergoing primary PCI or rescue PCI after thrombolysis
5. Cardiogenic shock
6. Inability to take adequate antiplatelet therapy (aspirin and clopidogrel)
7. Thrombocytopenia (platelet count <70 × 10^9^/l)

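### The single analysis set requires paired Virtual Histology for every end point, so a patient with usable grayscale IVUS can be dropped from the neointimal analysis and possibly from the primary

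*Protocol article*

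**What the plan says.** The Statistical analysis section of the protocol article sets one population for the primary and all secondary end points: randomised patients who took at least one dose and who "have IVUS and VH measurements at baseline and at the study end point". The condition is joint (IVUS and VH) and applies at both visits. The article gives no separate primary set and no exception for failed VH.

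Elsewhere the article describes what each modality is for:

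- Study end points defines the primary as the change in index-lesion plaque volume from baseline to 9 months and names no modality for it. VH appears in one secondary end point: "Plaque composition change by VH".
- Intravascular Ultrasound and Virtual Histology describes two outputs of one pullback: "During pullback, grayscale IVUS is recorded and raw radiofrequency data are captured at the top of the R wave", the latter being used to build the VH colour map. The same section assigns the stented lesion's neointimal growth to grayscale IVUS.
- Background presents VH as the technique that separates plaque into four tissue components.

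**The concern.** The set definition is stricter than the measurement plan. Neointimal growth is a grayscale measurement, yet a patient without paired VH is removed from it. VH is also not named as the method for the primary end point, so a patient whose plaque volume was measured at both visits may be removed because data for a different, secondary end point are missing.

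Two things would be at stake. The first is precision: the sample size leaves almost no margin above the number of evaluable patients it needs. The second is closeness to the randomised population: membership would depend on one more post-randomisation measurement, the 9-month VH, beyond what the end point itself needs.

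**Working it through.** **Inputs, all from the article**

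- Test: "based on an in-equality design and a two-sample, two-sided test".
- Error rates, SD and evaluable number: "Assuming a standard deviation of 8%, an α-level of 0.05 and a statistical power of 80%, 41 patients are required for each group".
- Difference: "to demonstrate a 5% difference in the mean plaque volume in a 10-mm segment".
- Allocation: patients "are randomised (1:1) to either cilostazol and probucol combination therapy or cilostazol monotherapy (control").
- Drop-out: "Making allowance for a drop-out rate of 30% increases the number of patients required for each group to 59".
- VH failure rate among patients with valid grayscale IVUS: not given. 5% and 10% are assumed below.

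**Step 1. Reproduce the plan's figure.** n per group = 2 × (1.96 + 0.842)² × (8/5)² = 2 × 7.849 × 2.56 = 40.2, rounded up to 41. With drop-out, 41 / 0.7 = 58.6, rounded up to 59 per group, 118 in total. Both figures reproduce.

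**Step 2. Margin.** 59 × 0.7 = 41.3 evaluable per group against 41 required. If the full 30% is used up by other losses, there is practically no reserve.

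**Step 3. Power if VH-only losses fall outside the 30%.** Two-sample t test (noncentral t), standardised difference 5/8 = 0.625, two-sided 0.05, starting from 2 × 41 = 82 evaluable patients:

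| Assumed VH-only loss | Patients lost | Evaluable (per group) | Power |
|---|---|---|---|
| 0% | 0 | 82 (41) | 79.8% |
| 5% | 0.05 × 82 ≈ 4 | 78 (39) | 77.8% |
| 10% | 0.10 × 82 ≈ 8 | 74 (37) | 75.6% |

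The starting value is 79.8% because the t test needs 41.2 per group for 80%; the plan's 41 matches the normal approximation.

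**Step 4. Which end points need VH, by the article's own text**

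| End point | Modality stated | Paired VH required by the set? |
|---|---|---|
| Plaque composition | VH | Yes, consistent |
| Neointimal growth | Grayscale IVUS | Yes, inconsistent |
| Plaque volume (primary) | None on its own; named with composition under IVUS and VH | Yes, not shown to be needed |

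**The case against.** **Source of plaque volume.** A reader might infer that plaque volume is a grayscale-only quantity, so that the rule certainly discards usable primary data. The article does not support that. The Abstract, the end of Background, Study Design and the imaging section all name plaque volume and composition together under IVUS and VH, and the imaging section specifies grayscale only for the stented lesion. If index-lesion volume is taken from the VH dataset, the condition is coherent for the primary and costs it nothing. This objection stands: for the primary, the point is conditional. It does not help the neointimal end point.

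**Failure mechanism.** One catheter and one pullback yield both outputs, and the article reports no case of VH failing alone. Lesions that are heavily calcified, tortuous or at a bifurcation are already excluded. This also stands in part: how often the situation arises is unknown. But the radiofrequency data are captured at the R wave and need their own recorder and reconstruction, so the rule has to say what happens when they are missing.

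**Size of the loss.** The components of the 30% allowance are not listed, so it may already cover VH failures; the planned sample size would then be unaffected. The power figures are also for an unadjusted test, whereas the primary analysis is an analysis of covariance on baseline. If baseline adjustment removes a share ρ² of the variance, it offsets the loss from 41 to 39 per group at ρ = √(1 − 39/41) = 0.22, and to 37 at ρ = √(1 − 37/41) = 0.31 (assumed correlations). So a shortfall in power cannot be claimed as a fact. Even so, if a plaque volume has been measured, dropping it gains nothing for the primary.

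**A common imaging set.** Using the same patients for volume and composition is a defensible convenience. It is a reason to report a common-set table as a supplement, not to remove observed values from the main analysis.

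**Conclusion.** The point holds in a limited form. For neointimal growth, the analysis-set rule conflicts with the article's own measurement plan, however plaque volume is derived. For the primary end point, the rule discards observed data only where plaque volume can be measured without VH, and the article leaves that open.

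The size is unknown because no VH failure rate is given. If 5% or 10% of evaluable patients were lost for this reason alone, and outside the drop-out allowance, unadjusted power would fall by 2.0 or 4.2 percentage points from 79.8%. If the allowance absorbs those losses, planned power is unaffected. The sample size itself is correct on its stated inputs.

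Nothing in the article shows that missing VH is related to treatment or outcome, so this is an avoidable loss of data and not a demonstrated bias. A correction is worth making because it takes little text.

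**What to change.** In the Statistical analysis section, for the imaging end points only, replace the joint IVUS-and-VH condition with three conditions, each applied to treated randomised patients:

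1. Plaque volume: an evaluable plaque-volume measurement at baseline and 9 months, whatever the VH status.
2. Neointimal growth: evaluable grayscale IVUS after PCI and at 9 months.
3. Plaque composition: VH at baseline and 9 months.

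State also which data supply plaque volume. If it is taken from the VH dataset, saying so makes condition 1 unambiguous.

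Do not extend this wording to every end point in the same sentence. Death, myocardial infarction and target vessel revascularization have no baseline measurement, so a requirement for paired measurements would make no sense for them; how those end points should be handled is a separate matter.

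The cost is a short text change and possibly different denominators in the volume, neointimal and composition tables, which a line under each table can explain. Sample size and model stay as they are. The volume and neointimal sets would still need both imaging visits, so the change removes only the extra VH condition and does not bring in patients without follow-up imaging.

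### Randomisation is stratified by site and diabetes, but the stated primary ANCOVA names neither; if they are prognostic, the analysis is mildly conservative and forgoes some precision

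*Protocol article*

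**What the plan says.** Under Study population and Randomisation, the article states: "The randomization is stratified by enrolling site and the presence of diabetes". The reason given there is to balance "major factors that might contribute to the primary end point". Study Design puts the number of sites at five, so site by diabetes gives ten strata.

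Under Statistical analysis, the primary model is given as: "The primary efficacy analysis will be performed using an analysis of covariance model, adjusting for baseline values". The fallback is: "If the data are not distributed normally, a nonparametric analysis of covariance analysis will be used". For the rest: "All continuous secondary efficacy variables will be analyzed using similar methods". None of these sentences mentions site or diabetes, and no other part of the article carries either factor into an analysis.

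One continuous secondary end point, listed under Study end points, is "Neointimal volume obstruction at index PCI target lesions". According to Intravascular Ultrasound and Virtual Histology, that lesion is imaged after PCI and again at 9 months.

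**The concern.** Stratified randomisation keeps the arms alike on the stratification factors. If those factors predict the outcome, the treatment estimate varies less from trial to trial than it would under simple randomisation. A model that leaves them out does not see this, because their variance stays in the residual and so in the standard error. The reported standard error then exceeds the true variability of the estimate, confidence intervals are too wide, and the actual type I error falls below 5%. The precision that the stratification makes available is not used.

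The trial needs only 41 evaluable patients per arm, and the Discussion itself names the small study population as a possible major limitation. A small gain at almost no cost is therefore worth having.

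The neointimal end point raises a related problem. There should be essentially no neointima immediately after stenting, so its baseline value is about zero in every patient and adjusting for it does nothing.

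**Working it through.** **Inputs from the article.** 1:1 allocation; five sites; stratification by site and diabetes; SD 8%; difference 5%; two-sided alpha 0.05; power 80%; 41 per group, 59 after 30% drop-out, 118 in total.

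**Assumed, because the article does not give it.** R2, the share of outcome variance explained by site and diabetes beyond baseline, is taken from 0 to 0.20.

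**Step 1: the plan's own figure.** n per group = 2 × (1.960 + 0.842)² × 8² / 5² = 40.19, rounded up to 41. Then 41 / 0.7 = 58.6, rounded up to 59, and 2 × 59 = 118. The figures reproduce. Power at 41 per group is 80.8% by the normal formula and 79.8% by the t test. This is an unadjusted calculation and takes no credit for any covariate.

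**Step 2: formula for the adjusted model.** SE = 8 × √(1 − R2) × √(2/41), and power = Φ(5/SE − 1.960).

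| R2 | SE | Power |
|---|---|---|
| 0 | 1.767 | 80.8% |
| 0.05 | 1.72 | 82.7% |
| 0.10 | 1.68 | 84.7% |
| 0.20 | 1.58 | 88.6% |

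This is an optimistic bound on the gain. It ignores the five degrees of freedom and the balance lost through drop-out. It also compares against a fixed 80.8%, whereas the baseline-only model gains slightly when prognostic strata are balanced.

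**Step 3: simulation.** 118 patients were randomised in permuted blocks of 4 within site-by-diabetes strata, with about 30% dropping out and a true difference of 5. Block size and a 30% diabetes prevalence are assumptions. Run 1 also assumed equal expected site sizes and R2 split equally between the two factors. Run 1 used 3,000 trials per cell and run 2 used 4,000. At 3,000 trials the Monte Carlo error on a power near 80% is √(0.8 × 0.2 / 3000) = 0.7 points.

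Power of the baseline-only model / the model with site and diabetes (change in points):

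| R2 | Run 1 | Run 2 | Run 3 |
|---|---|---|---|
| 0 | 79.6 / 78.3 (−1.3) | 79.2 / 78.2 (−1.0) | 79.2 / 78.3 (−0.9) |
| 0.05 | 78.7 / 79.4 (+0.7) | 79.5 / 80.9 (+1.4) | 78.8 / 79.7 (+0.9) |
| 0.10 | 80.7 / 83.2 (+2.5) | 79.7 / 81.8 (+2.1) | 81.2 / 82.7 (+1.5) |
| 0.20 | 81.8 / 86.9 (+5.1) | 81.0 / 86.1 (+5.1) | 80.8 / 86.3 (+5.5) |

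**Step 4: calibration.** In run 1 at R2 0.10, the baseline-only model reports a mean SE of 1.77, while the estimate's actual SD is about 1.66 to 1.71, so the SE is about 4% to 7% too wide (1.77/1.71 to 1.77/1.66). At R2 0.20 the comparison is 1.77 against about 1.65, or about 7%. Type I error of the baseline-only model was 3.5% (run 1) and 4.2% (run 3) at R2 0.10, and 3.8% and 3.7% at R2 0.20. With site and diabetes in the model, run 1 gave 4.3% to 5.5% over R2 0 to 0.20. Monte Carlo error at 5% is √(0.05 × 0.95 / 3000) = 0.4 points, so this agrees with the nominal level.

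**Step 5: degrees of freedom.** Five sites use 4 and diabetes uses 1, which makes 5 out of roughly 80.

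**The case against.** The strongest reply is that the article does not say baseline is the only covariate. It is a short journal paragraph, and a full covariate list may sit in a protocol or SAP that is not shown. That lowers certainty about what will be done. It does not remove the point, because the article does choose to state the model and its covariate, and leaves out the two factors it had singled out for the design. Baseline values most naturally means the outcome's own baseline. A wider reading might take in diabetes, but would not cover site.

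The second reply is that the benefit is conditional and may be small. This stands. The article says only that the factors might contribute to the end point. At R2 0 adjustment costs about a point, at 0.05 the models hardly differ, and the gain is material only near 0.20, a value the article does not support.

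A reader might infer that the trial is underpowered, biased or prone to false positives. The documents do not support that. The sample size rests on an unadjusted test, baseline-only power stays near 80% throughout, and the error is on the conservative side.

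A reader might also want to stratify the log-rank test by diabetes alone, or to add stent volume as a covariate for neointimal obstruction. Nothing in the article favours diabetes over site for the log-rank test. If obstruction is expressed relative to stent volume, as its name suggests, stent volume is already in the outcome. Finally, an all-zero neointimal baseline simply drops out and leaves a valid two-arm comparison, so that end point needs a clearer model but is not invalid.

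**Conclusion.** The design and the stated analysis do not match: the factors used to stratify are absent from the primary model as written. The consequence is a possible loss of precision, not an invalid test. With 30% drop-out, adding site and diabetes changes power by about −1 point at R2 0, +1 to +2 at 0.05, +2 to +3 at 0.10 and +5 to +6 at 0.20. These figures rest on an R2 that the article does not give, and on the assumed block size and diabetes prevalence. The change is worth making because the possible gain is larger than the possible cost, but the planned power does not depend on it.

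**What to change.** State the primary ANCOVA as treatment + baseline plaque volume + diabetes + site, with a rule fixed in advance for pooling small sites. Carry diabetes and site into the nonparametric fallback and into the continuous secondary analyses. For neointimal volume obstruction, use treatment + site + diabetes with no baseline term. If an SAP already specifies this, the article's sentence should be brought into line with it.

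The cost is a few lines of model specification, settled before unblinding, and five degrees of freedom. If the strata turn out not to be prognostic, that is about 1 point of power. No change to sample size, data collection or randomisation is needed.
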